#### Preoperative variables

These will be age, sex, clinical history, diagnosis, treatment, feeling of dump or twitch, limb weakness, serum PTH concentration, and thyroid-stimulating hormone (TSH), triiodothyronine (T3), thyroxine (T4), calcium and phosphate levels. Concomitant medication will also be recorded for oral supplementation with calcium and calcitriol soft capsules.

#### Intraoperative variables

Unilateral or bilateral surgery, duration of surgery, parathyroid gland numbers found and advertently removed, the color of the parathyroid glands.

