**Methods:**

In total, 280 patients will be enrolled in this study and randomly divided into two groups: 140 patients with transplanted parathyroid glands in the traditional sites (group A) and the other 140 transplanted in the novel sites (group B), close to the antecubital veins. The serum concentration of PTH and calcium ion from both forearms will be measured and monitored regularly for 12 months. The primary outcome of this trial will be the survival of grafted glands, defined as the ratio of PTH between the grafted vs. the non-grafted forearms being no less than 1.5. The secondary outcome is hypoparathyroidism, defined as the PTH level from the non-grafted forearms being less than 15 pg/ml (normal range 15–65 pg/ml).

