## Background

Parathyroid autotransplantation (PA) is an important technique for dealing with parathyroid glands removed in thyroidectomy and other neck surgeries [1, 2]. Unintentional parathyroidectomy is a major cause of postoperative hypoparathyroidism in total thyroidectomy with or without lymph node dissection [3, 4]. The incidence of unintentional parathyroidectomy during thyroidectomy has been shown to be 9–19% [5]. It has been reported that the number of remaining parathyroid glands in situ is a predictive variable for the rate of permanent hypoparathyroidism [6]. Although most parathyroid glands were preserved in situ in this study, permanent hypoparathyroidism was still observed frequently [6]. The incidence of permanent hypoparathyroidism could be up to 14.3% [7, 8] after thyroidectomy. PA has been reported to reduce the rate of permanent hypoparathyroidism [8, 9].

Our previous studies, recruiting 218 patients with thyroidectomy [10], indicated that approximately 17.5% of patients needed the partial tissue of one parathyroid gland for autotransplantation, and that 6.6% needed one or more integral parathyroid gland(s). However, there was no widely accepted, accurate method to evaluate the transplanted parathyroid glands. The currently popular method is to combine clinical symptoms and parathyroid hormone (PTH) serum concentration. However, this method cannot distinguish between the function of the remaining and transplanted parathyroid glands.

The PTH-gradient method, which compares serum PTH concentrations between the grafted and the non-grafted forearms, was originally applied to examine the function of transplanted parathyroid glands in patients with hyperparathyroidism [11]. A ratio of PTH from the grafted to non-grafted forearms of no less than 1.5 was considered to confirm successful PA [12]. It was mostly applied to monitor PTH in hyperparathyroidism patients with parathyroidectomy after PA [13, 14]. Rothmund et al. reported that the survival rate of PA with hyperparathyroidism was 31% (20 patients) [15], and Anamaterou et al. suggested that the survival rate was 45% in 19 patients using the ischemic-blockage Casanova test [16]. There are few reports regarding randomized controlled trials to evaluate the function of transplanted parathyroid glands using this PTH-gradient method.

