## Methods

### Study design

This is a prospective, randomized controlled trial to apply PA at the novel sites and to assess the survival rate of transplanted parathyroid glands in thyroidectomy patients. A 1:1 block randomization will be performed at the same clinical center and operations will be carried out by the same experienced surgeon in Tongji Hospital (Wuhan, China). The study has been approved by the Ethics Committee of Tongji Hospital, Tongji Medical College, Huazhong University of Technology Institutional Review Board with approval given on 25 June 2015 (reference number: TJ-C2015602) (Additional file 1).

In this single-center study, hospitalized patients with primary thyroidectomy in Tongji Hospital will be enrolled. Stochastic indicators were used to generate the random allocation sequence of the patients. Sequentially numbered containers were employed to implement the random allocation sequence and to conceal the sequence until interventions are assigned for implementation. Analysts in our study generated the random allocation sequence while care providers numbered the qualified participants. The surgeon assigned participants to interventions based on the condition of their parathyroid glands during thyroidectomy. All subjects, researchers in the laboratory and data analysts will be blind to the group classification.

Primary endpoint: the ratio of the serum PTH level from the grafted vs. the non-grafted forearm level is no less than 1.5 and the percentages of the 1.5 ratio in the experimental group are obviously higher than those in the control group. Since successful PA was defined as the ratio of the PTH level from the grafted to the non-grafted forearms as not less than 1.5, we set the primary endpoint in line with expert opinion, and the percentages of no less than the 1.5 ratio in the experimental group are obviously higher than those in the control group. 

Secondary endpoints: serum PTH less than 15 pg/ml, and lasting for more than 6 months, as well as a low serum calcium level requiring oral supplements to be taken. Duration of hospital stay will be documented according to hospital charts. During the 1-month to 12-month follow-ups after surgery, patients will be interviewed to assess for postoperative hypocalcemia.

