### Study participants

Those patients with parathyroid glands that are hard to preserve in situ, or that are mistakenly removed during primary thyroidectomy, will be screened for the inclusion criteria in our study, including malignant and non-malignant disease. Since 10–67% of adults have thyroid nodules on ultrasonography, 10–40% of which were reported as malignant [17, 18], both malignant and non-malignant thyroid diseases were taken into consideration at randomization and analysis. Participants aged from 18 to 65 years old will be enrolled, and those with hyperparathyroidism will be excluded (Fig. 2).

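### The primary 1.5-ratio comparison pools unilateral and bilateral operations in an unstratified test, although extent of surgery is recorded and bears on both endpoints

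*Protocol article*

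**What the plan says.** In the protocol article, Study participants describes the source population as "Those patients with parathyroid glands that are hard to preserve in situ, or that are mistakenly removed during primary thyroidectomy". The only further limits in that section are these: "Participants aged from 18 to 65 years old will be enrolled, and those with hyperparathyroidism will be excluded". Extent of surgery is not mentioned there. Intraoperative variables lists "Unilateral or bilateral surgery, duration of surgery, parathyroid gland numbers found and advertently removed, the color of the parathyroid glands", so one-sided operations are foreseen.

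The one clinical factor tied to allocation and analysis is diagnosis: "both malignant and non-malignant thyroid diseases were taken into consideration at randomization and analysis". Study design defines graft success by whether "the ratio of the serum PTH level from the grafted vs. the non-grafted forearm level is no less than 1.5". Data management and statistical analysis assigns that outcome to a chi-square test, with no stratum or covariate stated, and adds a Cox model for factors affecting graft survival without listing its covariates. Subgroup analysis, item 5, compares the primary outcome by the numbers of glands grafted and kept.

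Hypoparathyroidism is, in the abstract, "defined as the PTH level from the non-grafted forearms being less than 15 pg/ml". Study design adds a duration of more than 6 months and low calcium needing supplements. The Background states that "the number of remaining parathyroid glands in situ is a predictive variable for the rate of permanent hypoparathyroidism".

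**The concern.** After a one-sided operation the glands on the other side have not been operated on. The Background makes the number of glands left in place a predictor of permanent hypoparathyroidism, so by that logic these patients are at lower risk of the secondary endpoint whatever the graft does.

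The same native glands feed the denominator of the primary ratio. Two grafts with identical output can be classed differently because the patients' own glands differ. The trial aims at a more accurate reading of graft function, so this is a known source of variation in its main outcome. A recorded variable that captures part of it is not named in the main comparison. At stake are some precision in the primary comparison and the interpretability of the pooled hypoparathyroidism rate.

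**Working it through.** **1. The planned sample size.** Inputs from Sample size calculations: 45% vs 65%, two-sided alpha 0.05, power 0.90, 1:1 allocation.

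n = [1.960 × √(2 × 0.55 × 0.45) + 1.282 × √(0.45 × 0.55 + 0.65 × 0.35)]² / 0.20² = (1.379 + 0.883)² / 0.04 ≈ 127.9, that is 128 per arm.

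This reproduces the stated figure. The calculation treats each arm as one homogeneous population.

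**2. The bar set by the ratio.** Let S be PTH in the non-grafted arm and D the local increment from the graft.

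Ratio = (S + D)/S = 1 + D/S, so a ratio of at least 1.5 requires D ≥ 0.5 × S.

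| S (pg/ml) | D needed (pg/ml) |
|---|---|
| 10 | 5 |
| 15 (lower normal limit) | 7.5 |
| 40 | 20 |
| 65 (upper normal limit) | 32.5 |

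For example, with D = 10 (assumed) the ratio is 1 + 10/15 = 1.67 at S = 15, a success, and 1 + 10/40 = 1.25 at S = 40, a failure.

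**3. Possible dilution of hypoparathyroidism (illustration).** Assume a rate of 14.3% in bilateral patients (the Background's upper figure after thyroidectomy), about 0% in unilateral patients, and a unilateral share u. Pooled rate = 14.3% × (1 − u).

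- u = 0: 14.3%, or 140 × 0.143 ≈ 20 events per arm
- u = 0.2: 11.4%, or 16 events
- u = 0.5: 7.2%, or 10 events

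**4. Effect on the primary comparison (illustration).** Assume that bilateral patients succeed at 45% and 65%, and unilateral patients at f times those rates in both arms. The pooled rates are then 45% and 65% times (1 − u + u × f).

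| u | f | pooled rates | power at 128 per arm | n per arm for 90% power |
|---|---|---|---|---|
| 0.1 | 0.75 | 43.9% vs 63.4% | 0.883 | 136 |
| 0.2 | 0.5 | 40.5% vs 58.5% | 0.825 | 161 |
| 0.5 | 0.5 | 33.8% vs 48.8% | 0.686 | 225 |

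**5. What stratifying recovers.** With 1:1 allocation within strata, the size-weighted risk difference is unchanged. The null variance falls from p(1 − p) at the overall mean to the weighted average of p(1 − p) within strata.

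- u = 0.1, f = 0.75: 0.9 × 0.55 × 0.45 + 0.1 × 0.4125 × 0.5875 = 0.2470, against 0.53625 × 0.46375 = 0.2487. Reduction 0.7%.
- u = 0.2, f = 0.5: 0.8 × 0.55 × 0.45 + 0.2 × 0.275 × 0.725 = 0.2379, against 0.495 × 0.505 = 0.2500. Reduction 4.8%.
- u = 0.5, f = 0.5: 0.5 × 0.2475 + 0.5 × 0.1994 = 0.2234, against 0.4125 × 0.5875 = 0.2423. Reduction 7.8%.

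Stratifying removes the between-stratum noise. It does not undo the smaller pooled difference in step 4.

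**The case against.** The strongest reply is that the operative factor is the amount of native tissue, not the side of surgery. The Background names gland number, and item 5 of Subgroup analysis already looks at the primary outcome by glands grafted and kept. The Cox model's covariates are not listed and might include extent. So it cannot be said that extent is used nowhere. This stands, but neither item changes the pooled primary test, and the subgroup list does not reach hypoparathyroidism.

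A second reply is that patients with working native glands are the intended population, because the protocol wants a method that separates native from grafted function. That is a fair reason to enrol them. It is not a reason to ignore the variation they bring.

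Third, analysis detail often sits in a separate plan, and the flowchart (Fig. 2) is not shown and could narrow entry. But the article does state the primary test, and recording one-sided surgery implies that it is allowed.

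The arithmetic also invites readings that the document does not support:

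- The spread from 7.5 to 32.5 pg/ml (4.3-fold) is the width of the normal range. It is not a measured gap between unilateral and bilateral patients, and bilateral patients who keep most glands can span it too.
- The 14.3% is given for thyroidectomy with no extent stated. If it already mixes extents, step 3 counts the dilution twice.
- The 65% comes from preliminary data whose mix of operations is not given, so the power losses in step 4 may already be built in.

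**Conclusion.** The point holds as a loss of precision and clarity. With no stated limit on extent and an unstratified test, the plan pools patients who face different bars for the same ratio and probably different risks of hypoparathyroidism.

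A reader might infer that the comparison between arms is biased. It is not: allocation is randomised 1:1, and the choice of forearm site does not determine extent of surgery. What remains is noise, dilution and chance imbalance, and the test's error rate already allows for the last. A reader might also infer that hypoparathyroidism should be assessed only after bilateral surgery. That would set aside randomised patients and is not justified here.

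That the bar rises with S follows from the ratio's definition. That unilateral patients have higher S on average rests on the Background's statement about glands left in place. The size of the effect cannot be estimated from the document. The shares, relative success rates and near-zero unilateral event rate used above are assumptions. Under them, the precision gained by stratifying ranges from under 1% to about 8% of variance, so the improvement is modest but nearly free.

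**What to change.** In Data management and statistical analysis, replace the plain chi-square test for the primary outcome with a Cochran-Mantel-Haenszel test stratified by unilateral or bilateral surgery, or a logistic model with extent as a covariate. The envelope is opened when the graft is placed, so extent known at that moment is a legitimate pre-allocation factor. If it could still change afterwards, use the extent as it stood at opening.

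Keep hypoparathyroidism in all randomised patients as the main result, and report it by extent next to that result. Name extent beside gland numbers in Subgroup analysis.

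The cost is a few sentences and a little more analysis, with no new data and no change to treatment. The drawback is a small stratum if few unilateral cases are enrolled. The stratified test then gives it little weight, and its separate hypoparathyroidism figure would be descriptive only.

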#### Postoperative variables

PTH assays taken from the grafted and non-grafted forearms, serum calcium ion and phosphate levels, symptoms of limb numb or twitch, wound healing of the transplantation site, and duration of postoperative drainage.

### Outcome measures

Basal concentrations of PTH from both arms and the concentration of serum calcium will be obtained before and after surgery. Postoperative evaluation of symptoms and signs of hypocalcemia will be recorded as well as oral supplements with calcium and calcitriol. Two researchers will be assigned to record the examination results of participants, and to take blood samples.

### Criteria for discontinuing and quitting the trial

The following participants will quit this study: (1) any participant who develops breast cancer during the follow-up period, as the calcium homeostasis will be interrupted by the required breast cancer chemotherapy and hormone therapy; or (2) if the forearm is too fat to see the exact blood vessel arrangements. In general, no modifying allocated interventions for a given participant will be needed. Adverse events are seldom seen in this study, but sometimes graft-site infection may be observed and will be recorded.

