**Fig. 1 Fig1:**
[figure not shown]
Standard Protocol Items: Recommendations for Interventional Trials (SPIRIT) Figure: the schedule of enrollment, interventions, and assessments

The allocation envelope will be opened by the surgeon when conducting the interference. It will not be possible to mask the treatment allocation from the treating surgeon. Nevertheless, measures will be taken to minimize bias:The patients will not be informed regarding whether they will receive the novel site or the traditional site methodTo minimize detection and selection bias, the exact method of PA will not be documented in the medical recordsThe investigator performing the statistical analyses will be blinded to treatment assignments until the final analysis is completed

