### PA protocol

Patients will undergo operations in the supine position under general anesthesia. The removed parathyroid glands will be placed in sterile physiological salt solution at 4 °C until confirmed by the frozen-section diagnoses. The parathyroid glands will be sliced into 2–4-mm cubes and mixed with 0.5 cc sterile physiological salt solution in a 1-cc syringe. The parathyroid fragments will be subcutaneously injected into the non-dominant forearm with a 16-G needle [19].

The novel site method means choosing the graft site close to the antecubital veins, including the cephalic vein, the median cubital vein and the basilic vein. During the follow-up, blood samples will be taken from the vein near the graft site (Fig. 3), as well as from the opposite forearm. The traditional site method means general transplantation further away from the relevant antecubital veins. In Fig. 3, the novel sites are points A and B and the traditional are points C and D. All of the grafted forearms from the two groups will be pressed gently immediately after transplantation. The blood samples will be taken at five different time points: 3 days, 1 month, 3 months, 6 months and 12 months after transplantation.

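### Forearm vein visibility, which can be judged before surgery, is a reason to quit rather than an entry criterion, so patients may be removed after an unmasked surgeon knows the allocation.

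*Protocol article*

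**What the plan says.** All references are to the protocol article.

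- **Criteria for discontinuing and quitting the trial.** The list opens with "The following participants will quit this study" and has two entries. The first is "any participant who develops breast cancer during the follow-up period". The second applies "if the forearm is too fat to see the exact blood vessel arrangements". The first entry is tied to a period; the second has no time attached and no threshold.
- **Study participants.** Beyond the gland condition that leads to screening, the entry rules are: "Participants aged from 18 to 65 years old will be enrolled, and those with hyperparathyroidism will be excluded". Forearm build, body mass index and vein visibility are not mentioned.
- **Study design, text after Figure 1.** "The allocation envelope will be opened by the surgeon when conducting the interference", and "It will not be possible to mask the treatment allocation from the treating surgeon".
- **PA protocol.** "The novel site method means choosing the graft site close to the antecubital veins"; the traditional site lies further from those veins. Follow-up blood comes from a vein near the graft and from the other forearm, in both arms.

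**The concern.** A feature that is fixed and visible before the operation belongs among the entry criteria. Listed as a reason to quit, it applies to people already enrolled, and nothing requires the judgement to come before the envelope is opened. The surgeon, who is well placed to judge the forearm, then knows the arm and has no defined threshold to apply.

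The rule also bears differently on the two techniques. A novel-site graft cannot be placed as defined without locating the vein; a traditional graft can. The patients concerned are those in whom sampling near the graft may be hardest, and the primary endpoint is a PTH ratio obtained from that sampling. If they leave mainly the novel arm and would have done worse than average, the novel arm's success percentage rises without any effect of site.

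**Working it through.** **1. The plan's own sample size.** Inputs from Sample size calculations: 45% versus 65%, two-sided alpha 0.05, power 0.90.

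n per arm = [1.960·√(2·0.55·0.45) + 1.282·√(0.45·0.55 + 0.65·0.35)]² / 0.20² = 127.9, so 128. This matches the article. With 140 per arm the power is 0.924. The step from 128 to 140 allows for 1 − 128/140 = 8.6% loss, and loss to follow-up is the only reason given. The sample size is not in dispute.

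**2. When the rule can operate.** The sections leave two possibilities:

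- Consent is taken before surgery (Informed consent) and the envelope is opened at the intervention. A forearm judged between the two would be judged before allocation is known.
- The rule sits among reasons to quit, is absent from the entry criteria and carries no time. A forearm judged at grafting or later would be judged by someone who knows the arm.

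The text allows both. Only the first protects the randomised comparison.

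**3. Illustration of size.** From the document: a 45% success rate and 140 per arm. Assumed, because the document gives no figure: no true site effect, k patients removed from the novel arm only, and a proportion s of them who would have succeeded.

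Expected novel-arm successes before removal: 0.45 × 140 = 63. After removal the novel-arm rate is (63 − k·s)/(140 − k); control stays at 63/140 = 45.0%.

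Rejection probability, pooled-variance normal approximation: with d the difference in rates, SE₀ the pooled standard error, SE₁ the unpooled one and c = 1.960·SE₀,

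P = 1 − Φ((c − d)/SE₁) + Φ((−c − d)/SE₁).

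Worked case, k = 14 (10%), s = 0: novel rate 63/126 = 50.0%, d = 0.050, SE₀ = SE₁ = 0.0613, c = 0.1202. P = 1 − Φ(1.146) + Φ(−2.778) = 0.129.

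| Removed from novel arm | Would have succeeded | Novel vs control | Type I error |
|---|---|---|---|
| 7 (5%) | 35% | 45.5% vs 45.0% | 0.051 |
| 14 (10%) | 45% | 45.0% vs 45.0% | 0.050 |
| 14 (10%) | 35% | 46.1% vs 45.0% | 0.054 |
| 14 (10%) | 25% | 47.2% vs 45.0% | 0.065 |
| 14 (10%) | 0% | 50.0% vs 45.0% | 0.129 |
| 28 (20%) | 25% | 50.0% vs 45.0% | 0.124 |

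**4. Removal from both arms.** With 14 novel and 7 control patients removed, all failures, the rates are 63/126 = 50.0% and 63/133 = 47.4%, and the type I error is 0.071. With 14 and 10 it is 0.057. With equal removal it is 0.050.

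Equal removal costs only power. At 45% versus 65% among those remaining, power falls from 0.924 to 0.911, 0.896, 0.878 and 0.858 for 5%, 10%, 15% and 20% removed per arm.

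**The case against.** The other side has a good deal to say.

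- **Timing is not stated.** The breast-cancer entry is expressly placed in follow-up; the forearm entry is not. A consented patient could be found unsuitable before the envelope is opened, and the fault would then be only a misplaced entry criterion. This stands: removal after allocation is permitted by the text, not asserted by it.
- **The arms may lose patients equally.** Sampling near the graft is required in both groups, so poor veins matter in both. This also stands. A reader might infer that removals will fall mainly in the novel arm; the definition of the novel site makes that plausible, but the protocol neither says so nor gives a frequency.
- **The larger error rates are extreme.** The 0.129 assumes that every removed patient would have failed and that none leaves control. Under no site effect, difficulty in placing the graft cannot itself lower success; only sampling difficulty can, and that is shared. Bias therefore needs lopsided removal. This is accepted, and it is why the milder cases are shown beside it.
- **Breast cancer.** A reader might class this rule with the forearm rule. Incident breast cancer has no evident link to graft site and the protocol gives its reason, so it does not support this point.
- **Analysis set.** A reader might infer that patients who quit are dropped from the analysis. The article does not say so, and naming the analysis population may be left to the SAP. That silence is no finding. An SAP cannot, however, supply PTH ratios for patients whom the protocol has taken out of follow-up.

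What survives is that a baseline feature is listed as a reason to quit, with no threshold and no requirement to judge it before an unmasked surgeon learns the arm.

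**Conclusion.** The point holds in a limited form. The entry criteria and the quitting criteria do not fit together, and the wording leaves room for removal that depends on the arm and is related to outcome. The document does not show that this will happen.

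The size cannot be computed from the protocol. If 10% were removed from the novel arm only, the type I error would be about 0.054 to 0.065 when 35% to 25% of them would have succeeded, and 0.129 when none would. Equal removal leaves it at 0.05. These figures rest on an assumed removal fraction, an assumed success rate among those removed, a 45% rate in both arms and a normal approximation. To conclude that the primary comparison is already invalid would go beyond the text.

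Severity SHOULD-FIX, confidence moderate: the consequence is uncertain, but patients lost in this way cannot be recovered later and prevention is nearly free.

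**What to change.** 1. Reconcile Study participants with the quitting criteria: list visibility of the forearm veins as an eligibility item, assessed and recorded before the envelope is opened.
2. Delete the forearm entry from the quitting criteria.
3. State that every randomised, grafted patient is followed and analysed in the allocated arm.

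The cost is a wording change, one preoperative checklist item and a slightly narrower entry population. The calculated 128 per arm, and 140 with the allowance, are unchanged.
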